## Abstract

**Background:**

Robust data on the contemporary management of atrial fibrillation (AF) patients in China are limited. Importantly current practice in AF management has changing dramatically in recent years. Data from a large registry study will enable us to evaluate the uptake and outcomes with different therapies in a large Chinese AF population.

**Methods/Design:**

The Chinese Atrial Fibrillation Registry study (CAFR) aims to enroll 20,000 consecutive atrial fibrillation (AF) patients from 32 tertiary and non-tertiary hospitals in Beijing, China, and follow up these patients every 6 months until 2020. Key data collected includes basic sociodemographic information, symptoms and signs, medical history, results of physical examination and laboratory test, details of treatments and personal insurance status. For patients who consent, 5 ml of blood sample will be stored at −80 °C for future analyses of biomarkers. At each 6 month follow up visit, data relating to clinical outcomes will be collected. Data from a randomly selected 10 % of patients will be internally validated with their raw source data. Ischemic stroke events will be adjudicated by an independent endpoint committee.

**Discussion:**

CAFR will be one of the largest registries of Asian AF patients (and the largest in Chinese AF patients), as well as providing the longest follow up. This study would provide a valuable opportunity for ‘real world’ clinical epidemiology with insights into the uptake (and outcomes) of contemporary AF management.

**Trial registration:**

Chinese Clinical Trial Registry ChiCTR-OCH-13003729. Registered 22 October 2013.

**Electronic supplementary material:**

The online version of this article (doi:10.1186/s12872-016-0308-1) contains supplementary material, which is available to authorized users.

## Background

Atrial fibrillation (AF) is the most common sustained cardiac arrhythmia and carries an increased risk of stroke, hospitalization, and mortality [1, 2]. It is estimated that at least 10 million patients in China suffer from AF [3]. With the ageing population and associated prevalence of other cardiovascular diseases, the burden of AF is projected to increase even further in China.

Although AF has been identified as a major risk factor for stroke, recommendations on anticoagulation therapy in Asian population are inconsistent in several aspects, including criteria for anticoagulation and the intensity of warfarin use. There is a perception that Asians are more prone to bleeding (especially intracranial bleeding) on warfarin [4, 5] and some guidelines even recommend that the Asian population should target a lower international normalized ratio (INR) range (eg. 1.6–2.6) when warfarin is used [5, 6]. Despite limited evidence supporting this practice, Chinese doctors tend to be conservative when prescribing oral anticoagulation (OAC) therapy for AF patients, reflected by an extremely low usage of OAC. When warfarin is prescribed, a lower INR is usually targeted. Indeed, limited data on quality of anticoagulation control (as reflected by time in therapeutic range, TTR) are available from Asian cohorts, despite TTR being closely related to the efficacy and safety of warfarin [7].

Thus, real world data may provide additional evidence to guide our practice when evidence from randomized trial is less likely to be obtained. In addition, the treatment of AF is changing in many ways in China. For example, catheter ablation is provided in majority of tertiary hospitals despite the shortage of evidence supporting its effectiveness on patient centered outcomes. Non-Vitamin K antagonist oral anticoagulants (NOACs) are increasingly prescribed whilst data of effectiveness and safety of these agents is more limited among Chinese population. Left atrial appendage occlusion was introduced in China in the last 2 years and real world data would be valuable in evaluating the effectiveness of this new technique.

Third, we recognize that genetic susceptibility contributes to the development of some diseases and the patients’ response to therapy [8]. Indeed, some patients with paroxysmal AF will not progress to persistent AF for many years while others progress more quickly. Stroke also happens in some AF patients without any known risk factors. Incorporating phenotype and genotype studies will provide the opportunity for better understanding of AF as a disease entity and for personalized treatment.

The Chinese Atrial Fibrillation Registry study (CAFR) is a prospective registry study launched in August 2011 and is still ongoing. Herein we reported the rationale, design of this study and current status of the database.

### Research objectives

CAFR aims to provide evidence for clinical practice based on real world data. The main objectives are as follows: (i) to compare and validate current risk scores for stroke and bleeding risk assessment in Chinese AF patients; consequent upon this, to improve current risk prediction models using phenotype and genotype data; (ii) to study factors associated with anticoagulation under-use, variation in stroke prevention practice and progress over the study period in typical tertiary and non-tertiary hospitals; and (iii) to report on safety and long term effectiveness of AF ablation therapy, and compare the effectiveness of ablation and medical therapy in reducing death and thromboembolic events, using propensity score matched cohorts.

The following additional exploratory analyses will also be considered: (i) description of effectiveness and safety of NOACs and left atrial appendage closure among the Chinese AF population; and (ii) assessment of biomarkers associated with AF progression from paroxysmal to persistent AF, and development of complications.

## Methods/Design

### Study setting

Thirty two tertiary and non-tertiary hospitals at where the majority of AF patients in Beijing are managed, have agreed to participate in this study. The characteristics of participating hospitals are listed in Table 1.

**Table 1 Tab1:** Characteristics of participating hospitals

	Tertiary hospitals	Non-tertiary hospitals
No of hospitals	20	12
No. of beds for cardiovascular disease, Median (IQR)	78 (59–120)	46.5 (12–80)
AF ablation facilities	18/20 (90 %)	0/12 (0 %)

### Patient inclusion and exclusion criteria

Patients aged 18 years or older with a documented AF as confirmed by 12 leads ECG, pacemaker/ICD electrocardiogram, or Holter ECG (duration of AF episode least 30 s) are eligible for this study. Patients with transient AF caused by reversible cause (e.g., cardiac surgery, pulmonary embolism, untreated hyperthyroidism) or combined with other serious diseases with a life expectancy < 1 year were excluded. All patients with the diagnosis of AF who are under the care of cardiologists or general physicians in the participating hospitals, and provided informed consent will be enrolled, from both outpatient and inpatient settings. Each hospital maintained an admission record to provide evidence of whether there was selection bias, by comparing the mean age, sex and comorbidities of enrolled and non-enrolled patients. Enrollment will cease when the target of 20000 patients is achieved.

### Clinical data collection

Key data elements and definition of each variable were in line with the ACC/AHA recommendation on AF clinical data standards [9] and international peer studies [10] to facilitate cross-comparison of results between different registries. The following data were collected for each patient enrolled: basic socio-demographic information, symptoms and signs relating to AF, medical history, results of physical examination and laboratory test and patient self-reported quality of life (using a validated Chinese version of AFEQT questionnaire). For patients undergoing ablation therapy, detailed procedure related information is also collected, including the pathway of ablation, achievement of conduction block, time consumed and peri-procedure complications.

Each enrolled patient will be followed up every 6 months by trained staff, at outpatient clinic or through telephone interview. Information relating to medical therapies, health-care utilization, and clinical outcomes will be collected during follow up. Definition of the major outcome events are provided in Table 2. Every patient will be followed up until 2020. The questionnaires used for data collection in study are provided in appendix. All the data were entered into a specific electronic data capture system.

**Table 2 Tab2:** Outcomes collected and associated definitions

Outcomes	Definitions
Primary outcome	
Composite outcome of any of the following events: all-cause mortality, non-fatal ischemic stroke and peripheral embolism.	All-cause mortality: All deaths regardless of etiology
	Non-fatal Ischemic stroke: Documented stroke or cerebrovascular accident consisting of acute loss of neurological function caused by an ischemic event with residual symptoms at least 24 hours after onset.
	Peripheral embolism: Abrupt vascular insufficiency associated with clinical and radiological evidence of arterial occlusion in a vascular bed other than the cerebrovascular system in the absence of other likely mechanisms (e.g., atherosclerosis).
Secondary outcomes	
Component of the primary composite outcome including: 1) all-cause mortality; 2) non-fatal stroke or peripheral embolism.	As above
Intracranial hemorrhages	Bleeding into or around the brain, including 1) Hemorrhagic conversion of a primary ischemic stroke; 2) Subarachnoid hemorrhage; 3) Intra-cerebral hemorrhage; 4) Other (including subdural and epidural hematomas);
Major bleeding	Bleeding leads to 1) Transfusion of at least 2 units of whole blood or erythrocytes; 2) Requiring hospitalization or surgery; 3) Resulting in permanent disability; 4) Involving a critical anatomic site (retroperitoneal, pericardial, intra-spinal, intracranial, non-traumatic intra-articular, or intra-ocular bleeding associated with abrupt deterioration of visual acuity).

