### Statistical analysis

The CHADS_2_ schema and CHA_2_DS_2_-VASc schema will be compared and validated in these Chinese AF patients, after excluding patients receiving anticoagulation therapy or ablation therapy during follow up. Logistic regression will be used to evaluate the predictive value of the various risk schemata in discriminating between patients who develop the outcome of interest and those who do not. The c-statistic will be estimated to determine the predictive ability for stroke of each schema. The 95 % confidence interval will be estimated for the c-statistic using a non-parametric bias-corrected bootstrapping method. To assess the effect of individual risk factors on the occurrence of events, multivariable logistic regression will be used with the baseline covariates as independent variables. According to the result of the multivariable logistic regression analysis, the score for each risk factor will be adjusted for the best fitted classification schema. If necessary, new risk factors may also be added to generate a new stroke risk classification schema for Chinese AF population. The new schema will be validated on the validation population and the C-statistics will be calculated using the new risk schema. In addition, the net reclassification index will also be used to evaluate predictive value of the prognostic score.

To compare the ablation and non-ablation therapies, propensity score matching for receiving catheter ablation will be calculated for each patient based on a multivariable logistic regression model. Baseline characteristics variables which are assumed to be associated with the probability of having catheter ablation will be included in the model as independent variables. Based on the propensity scores, ablation and non-ablation patients will be matched on a 1:1 basis with a combination of the nearest neighbor algorithm and caliper algorithm [12]. For each ablation patient, a non-ablation patient with the smallest propensity score difference, and smaller than 0.02, will be matched without replacement. Patients not matched will be excluded from the analysis.

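### The only thromboembolic outcome reported apart from death counts non-fatal stroke alone, so fatal ischemic strokes are missing from that component of the ablation comparison

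*Protocol article*

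**What the plan says.** Table 2 (Clinical data collection) gives the primary composite as "all-cause mortality, non-fatal ischemic stroke and peripheral embolism". Its only definition of ischemic stroke opens "Non-fatal Ischemic stroke: Documented stroke or cerebrovascular accident consisting of acute loss of neurological function caused by an ischemic event" and goes on to require that symptoms remain a day after onset. Mortality is "All deaths regardless of etiology". The secondary outcomes split the composite into all-cause mortality and "non-fatal stroke or peripheral embolism", the latter defined by reference back to the entries above. No stroke death or other cause-specific death is listed.

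Objective (iii) in Research objectives is to "compare the effectiveness of ablation and medical therapy in reducing death and thromboembolic events".

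Elsewhere the non-fatal limit does not appear:
- Data management and quality control sends every reported ischemic stroke and peripheral embolism to the endpoint committee.
- Statistical analysis names the composite with plain stroke. For the risk scores it says "The c-statistic will be estimated to determine the predictive ability for stroke of each schema", and it describes the regression as "discriminating between patients who develop the outcome of interest and those who do not".
- Sample size calculation uses ischemic stroke plus intracranial hemorrhage.

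**The concern.** Inside a composite with all-cause death, limiting stroke to the non-fatal kind is sound: it avoids counting one event twice and loses nothing. Once the stroke component stands alone, the same limit makes the outcome depend on two things, having a stroke and surviving it. A treatment or patient mix that makes strokes less often fatal then moves events into the outcome and looks harmful. One that makes them more often fatal looks protective.

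The ablation and non-ablation groups are not randomised, and the sample size section itself calls them quite different, so equal case fatality cannot be taken for granted. At stake is how the thromboembolic part of objective (iii) is read when it is reported apart from death.

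**Working it through.** **1. Where a fatal ischemic stroke is counted under Table 2**

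| Outcome | Fatal ischemic stroke counted? |
|---|---|
| Primary composite | Yes, as a death |
| Secondary: all-cause mortality | Yes, mixed with all other deaths |
| Secondary: non-fatal stroke or peripheral embolism | No, by its label |
| Any stroke-death outcome | None listed |

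The 24-hour clause adds a second gap. It has no alternative for death, so a stroke that kills within a day fails the definition even if the non-fatal label is removed. By contrast, the Table 2 entry for intracranial hemorrhage carries no non-fatal limit.

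**2. Effect of unequal case fatality (illustration)**

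Let p be the true ischemic stroke risk and f the fatal share of strokes. The component observes p(1 − f), so the observed ratio is the true ratio × (1 − f for ablation)/(1 − f for controls). None of these inputs is in the documents. Assume p = 8% in both groups, f = 25% in controls and 15% after ablation:
- controls: 8% × 0.75 = 6.0%
- ablation: 8% × 0.85 = 6.8%
- ratio: 6.8/6.0 = 1.13, where the true ratio is 1.00

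With the two fatalities exchanged, the ratio is 6.0/6.8 = 0.88, a false benefit. In the first case the strokes left out are 2.0% in controls and 1.2% after ablation. They reappear in all-cause mortality, and non-fatal plus fatal returns 8.0% in each group. The composite therefore carries no false difference from this source.

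**3. Effect of equal case fatality (illustration)**

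The ratio is then unchanged, but events are lost. To give a scale, start from the plan's own calculation: 10% against 7% at five years, α = 0.05, 90% power, 1:1 matching. Assuming a two-sided test with pooled variance under the null,

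n = [1.960 × √(2 × 0.085 × 0.915) + 1.282 × √(0.10 × 0.90 + 0.07 × 0.93)]² / 0.03² = 1814 per arm.

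The stated 1800 is reproduced; power at 1800 is 89.8%.

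That calculation concerns ischemic stroke and intracranial hemorrhage, with no non-fatal limit, so it is not itself at fault. If an outcome with these rates were limited to non-fatal events, with the same assumed f in both arms:

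| Assumed f | Rates | n per arm for 90% power | Power at 1800 |
|---|---|---|---|
| 5% | 9.5% v 6.65% | 1919 | 88.1% |
| 10% | 9.0% v 6.3% | 2035 | 86.2% |
| 20% | 8.0% v 5.6% | 2311 | 81.6% |
| 30% | 7.0% v 4.9% | 2665 | 75.9% |

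**4. Prediction models**

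The analysis text speaks of stroke and of an outcome of interest, without reference to Table 2. Table 2 holds the only stroke definition in the article. The two passages neither apply the non-fatal limit to prediction nor rule it out.

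**The case against.** The strongest reply is that the split is coherent. The secondary outcomes are presented as components of the composite, and death plus non-fatal events divides it without overlap. The planned ablation comparison is on the composite, which matches the wording of objective (iii) and loses no fatal stroke. All of this stands for the primary analysis. It does not rescue the component: a reader who wants the thromboembolic effect apart from death has only the non-fatal outcome, and the mortality component cannot show which deaths were strokes.

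Second, the body of the stroke definition contains no survival condition. A patient who dies of a stroke some days later meets the text, and no window for fatal is given. So it is the label that excludes such patients, and the true loss could lie anywhere between strokes fatal within a day and all fatal strokes. That stands as a limit on the size of the problem.

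Third, the numbers are assumed. This also stands: the 1.13 comes wholly from the assumed difference in fatality.

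Two stronger readings are tempting and should not be drawn. A reader might infer that the prediction models code fatal strokes as no stroke, so that 200 events over 20 variables become 180 to 140, or 9 to 7 per variable, at 10–30% fatality. The article does not say that the prediction outcome is non-fatal stroke, and its 200 is a minimum number of outcome events however they are defined. A reader might also infer that the primary composite or the 1800 per arm is wrong. Neither is.

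**Conclusion.** The point holds for the stand-alone thromboembolic component. As Table 2 is written, a fatal ischemic stroke is recorded only as a death, and the component depends on surviving the stroke. Bias in the ablation comparison of that component requires case fatality to differ between the groups; with equal fatality the cost is lost events and precision. Its size cannot be fixed from the documents, and the figures above only show direction and scale under stated assumptions. The primary composite, the 1800 per arm and the 200 events are unaffected. For prediction, the supportable statement is only that the stroke outcome is not tied to a definition. This is a cheap improvement to a secondary outcome that serves a main objective, and it should be made.

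**What to change.** - Define the secondary component as ischemic stroke (fatal or non-fatal) or peripheral embolism.
- Reword the stroke definition so that it is met by symptoms still present 24 hours after onset or by death from the stroke.
- Treat death from other causes as a competing event when this component is analysed.
- State that the risk-score validation and the new prediction model use the same fatal-or-non-fatal definition.
- Leave the primary composite as it is.

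The cost is a line in Table 2 and a sentence in Statistical analysis. The endpoint committee already receives all reported ischemic strokes, so little new work should follow; the point to check is that a death caused by stroke reaches it as a reported stroke and not only as a death. The small downside is that a fatal stroke then counts in both the mortality and the thromboembolic components, so the two no longer add up to the composite. A footnote should say so.

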### Blood sample for future analysis

Five milliliter venous blood sample will be collected from patients with consent. The sample will be centrifuged. Plasma and blood cells will be separately stored at −80 °C refrigerators. Standard operation procedures for blood collection, processing and archiving are in line with the International Society for Biological and Environmental Repositories’ Best Practices for Repositories [11]. FreezerPro® is used for web-based management of frozen samples and information of sample will be linked to corresponding clinical data.

### Data management and quality control

All clinical data will be captured via a web-based electronic data capture (EDC) system. Investigators will enter and edit the data via a secure network, with secure access features. Variables related to the answer of main aims are mandatory to be entered. The database also had function of range and logic check. Source material will be kept in hospital for further monitoring and auditing. The quality control team will review all the data collected case by case and send queries when applicable.

A random selection of 10 % cases will have their raw data validated, for baseline data collection and during each follow up. All reported ischemic stroke and peripheral embolism events will be adjudicated by an independent endpoint committee.

### Ethical considerations

Ethics approval was obtained from the Human Research Ethics Committees at Beijing Anzhen Hospital. Ethic review boards in each participating hospital agreed their participation. The data collected will be held centrally in a secure database, only de-identified information can be used for analysis. Informed consent from individual patients was sought for their agreement to participate in long-term follow-up and usage of their blood sample for further analysis. The study was performed according to the ethical principles for medical research involving human subjects specified in the Declaration of Helsinki.

### Statistical analysis

The CHADS_2_ schema and CHA_2_DS_2_-VASc schema will be compared and validated in these Chinese AF patients, after excluding patients receiving anticoagulation therapy or ablation therapy during follow up. Logistic regression will be used to evaluate the predictive value of the various risk schemata in discriminating between patients who develop the outcome of interest and those who do not. The c-statistic will be estimated to determine the predictive ability for stroke of each schema. The 95 % confidence interval will be estimated for the c-statistic using a non-parametric bias-corrected bootstrapping method. To assess the effect of individual risk factors on the occurrence of events, multivariable logistic regression will be used with the baseline covariates as independent variables. According to the result of the multivariable logistic regression analysis, the score for each risk factor will be adjusted for the best fitted classification schema. If necessary, new risk factors may also be added to generate a new stroke risk classification schema for Chinese AF population. The new schema will be validated on the validation population and the C-statistics will be calculated using the new risk schema. In addition, the net reclassification index will also be used to evaluate predictive value of the prognostic score.

To compare the ablation and non-ablation therapies, propensity score matching for receiving catheter ablation will be calculated for each patient based on a multivariable logistic regression model. Baseline characteristics variables which are assumed to be associated with the probability of having catheter ablation will be included in the model as independent variables. Based on the propensity scores, ablation and non-ablation patients will be matched on a 1:1 basis with a combination of the nearest neighbor algorithm and caliper algorithm [12]. For each ablation patient, a non-ablation patient with the smallest propensity score difference, and smaller than 0.02, will be matched without replacement. Patients not matched will be excluded from the analysis.

Unadjusted event rates for the composite primary outcome of time to first all-cause mortality, stroke and peripheral embolism for the propensity-matched ablation and non-ablation groups will be estimated using the Kaplan-Meier method and compared between groups with the log-rank test. As sensitivity analyses, the inverse probability of treatment weighting using propensity score will also be used to compare the survival distributions between ablation and non-ablation group.

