### Sample size calculation

For the objective of developing the optimal risk prediction model for Chinese AF population, a minimum of 200 events (i.e. 10 times of the variable number) are required to accommodate 20 variables in the prediction model. The analysis is planned to be done in 2015 to accumulate enough events for analysis. For that purpose, about 5000 patients without anticoagulation therapy are required for an evenly splitted training cohort and validation cohort. For the objective of evaluating the effectiveness of ablation therapy, the following assumption is made: the accumulate ischemic stroke and intracranial hemorrhage is 10 % in optimally anticoagulated patients and 7 % in ablation patients in five years, 1800 matched patients in each arm are required to provide 90 % power to detect the difference (α = 0.05). As those two groups of patients are quite different, we amplified the sample size by 3 times to guarantee enough matched patients. In total, 16000 patients are required for the main analyses and considering a possible 20 % withdraw and loss of follow up, we up round the sample size to 20000.

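### The cohort for validating and deriving the stroke score is defined by treatment received during follow-up, so it is selected partly on the future and can delete strokes with the patients who had them

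*Protocol article*

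**What the plan says.** In the protocol article, the Statistical analysis section sets the population for the risk-score work: the existing scores are compared "after excluding patients receiving anticoagulation therapy or ablation therapy during follow up". The time window is follow-up. The section does not refer to treatment status at enrolment, and does not distinguish treatment begun before an event from treatment begun after one.

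The model is binary: "Logistic regression will be used to evaluate the predictive value of the various risk schemata in discriminating between patients who develop the outcome of interest". Discrimination is the main performance measure: "The c-statistic will be estimated to determine the predictive ability for stroke of each schema". The same paragraph then re-weights the risk factors and may add new ones to form a score for Chinese patients.

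The Sample size calculation section describes the set only loosely: "about 5000 patients without anticoagulation therapy are required for an evenly splitted training cohort and validation cohort". It gives no time point for being without anticoagulation. It bases the size on events: "a minimum of 200 events (i.e. 10 times of the variable number) are required to accommodate 20 variables in the prediction model".

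The Clinical data collection section has 6-monthly contacts and states: "Information relating to medical therapies, health-care utilization, and clinical outcomes will be collected during follow up". Treatment begun after a stroke would therefore be recorded, and would meet the exclusion.

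**The concern.** Whether a patient belongs to the cohort is known only after follow-up, and can depend on the outcome. Two groups leave, with opposite effects.

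- **Treated after a stroke.** The patient was untreated and at risk when the stroke occurred, which is exactly the event the score should predict. Later anticoagulation removes patient and stroke together. Observed risk falls.
- **Treated while event-free.** The patient contributed untreated, event-free time before starting. All of it is discarded. Observed risk among those left rises. If higher-risk patients start more often, the mix of scores changes as well.

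A logistic model keeps or drops whole patients. It has no time axis on which to keep untreated time and stop counting at treatment start.

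This is main objective (i) of the registry. At stake are the absolute risks attached to each score level, and the weights of any new score. The Background describes conservative prescribing and very low anticoagulant use, so a wrong estimate of untreated stroke risk would matter to readers.

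**Working it through.** **1. The plan's own figure.** Events required: 10 per variable × 20 variables = 200. This reproduces exactly. The implied risk is 200/2,500 = 8% if the 200 events belong to the training half, or 200/5,000 = 4% if they span both halves. The article does not say which. The concern is therefore the analysis set, not the arithmetic.

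**2. First mechanism alone: strokes followed by treatment.** Let f be the share of stroke patients who later start anticoagulation or have ablation. The document gives no value, so f is assumed to lie between 0 and 50%. Suppose the 200 events are counted before the exclusion. Then events kept = 200 × (1 − f), and observed risk = 200(1 − f) / (n − 200f).

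| f | Events kept | Events per variable | Risk, n = 2,500 (true 8%) | Risk, n = 5,000 (true 4%) |
|---|---|---|---|---|
| 0 | 200 | 10 | 8.0% | 4.0% |
| 10% | 180 | 9 | 180/2,480 = 7.3% | 180/4,980 = 3.6% |
| 30% | 140 | 7 | 140/2,440 = 5.7% | 140/4,940 = 2.8% |
| 50% | 100 | 5 | 100/2,400 = 4.2% | 100/4,900 = 2.0% |

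**3. Both mechanisms together.** All of the following is assumed, for illustration: a binomial(8, 0.3) score; a yearly stroke hazard of 0.035 × 1.45^(score − 2.4); entry spread evenly over 4 years; treatment starts unrelated to the score. The true rate is then 3.9 per 100 patient-years. The plan's rule was applied to a large simulated cohort.

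| Treated after stroke | Event-free starts per year | Observed rate per 100 patient-years |
|---|---|---|
| 0 | 0 | 3.9 |
| 0 | 5% | 4.2 |
| 0 | 10% | 4.4 |
| 10% | 10% | 4.0 |
| 30% | 0 | 2.8 |
| 50% | 0 | 2.0 |

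The second and third rows lie above the truth. In the fourth the two biases nearly cancel. The last two lie below it. As a check on those two: 3.9 × 0.7 = 2.7 and 3.9 × 0.5 = 1.95. The simulated values are slightly higher because the deleted patients' time leaves the denominator too.

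Share of strokes kept = (1 − f) × the share not preceded by a treatment start, which is about 0.94 at 5% per year and 0.88 at 10%. With f = 30% and 5% per year: 0.70 × 0.94 = 66%. With f = 50% and 10% per year: 0.50 × 0.88 = 44%.

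**4. The alternative.** In the same simulation, keeping every patient untreated at baseline and censoring at treatment start only when it precedes the stroke gives 3.88 to 3.90 throughout.

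**5. Discrimination.** In the setting of step 3, the c-statistic stays at 0.634 to 0.642 against a true 0.636. A separate illustration uses a 7-level score with true risk 8% and true c = 0.662, and lets the deletion of strokes depend on the score:

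| Strokes deleted | Observed risk | c-statistic |
|---|---|---|
| 30% at every score | 5.7% | 0.662 |
| Rising with score, 10% to 50% | 5.5% | 0.618 |
| Falling with score, 50% to 10% | 6.0% | 0.702 |

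**The case against.** **The wording may mean treatment while still at risk.** The sponsor could have meant anticoagulation before an event, and a condensed article may leave the operational definition to the full protocol or analysis plan. This stands in part: the text does not say outright that strokes followed by treatment are deleted. But the article does more than omit a detail. It states a rule and names follow-up as its window. The intended reading would also not cure the problem, because removing event-free starters as whole patients still selects on later treatment and discards untreated time.

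**A reader might infer that stroke rates are simply biased downward.** The document does not support that. The rule also removes event-free starters, which pushes the rate up, and the article gives neither share.

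**A reader might infer that the 200 events fall to 100 to 140.** That needs 30 to 50% of stroke patients to be treated afterwards, a share that appears nowhere in the document; the Background's account of very low anticoagulant use gives it no support. The plan also calls for "a minimum of 200 events" and times the analysis so that enough accrue. The 200 can be read as a count within the analysed set, in which case exclusions mean longer accrual or more patients. With 17,467 enrolled by June 2015, that may be affordable.

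**Discrimination may be unharmed.** This stands if post-stroke treatment is unrelated to the score. It does not if treatment depends on age or comorbidity, which the score contains.

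**Conclusion.** The point holds in a limited form and should be fixed. As written, the exclusion selects the cohort for a main objective on post-baseline treatment that can result from the outcome, and no other section restricts it.

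The direction of the net bias cannot be stated from the document. Under the illustrative assumptions the observed rate runs from about 2.0 to about 4.4 per 100 patient-years against a true 3.9, and strokes kept run from 100% to about 44%. These ranges rest on 0 to 50% treated after stroke, 0 to 10% per year starting event-free, and an assumed score distribution and hazard. They show what the rule can do, and do not estimate what it did. The loss of events should be read in the same way. Bias in the c-statistic is possible in either direction, but only if treatment after stroke depends on the score.

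Extra enrolment would restore the event count but would not remove the selection.

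**What to change.** 1. Define the cohort at enrolment: no anticoagulation and no prior ablation. Table 3 shows that warfarin use, antithrombotic use and history of radiofrequency ablation are recorded, with about 1% missing or less.
2. Keep every such patient. Count each stroke that precedes any treatment start, whatever treatment follows it.
3. Censor at the start of anticoagulation, ablation or left atrial appendage closure, whichever comes first, and only when it precedes the event.
4. Replace the logistic regression with a time-to-event model and a c-index adjusted for censoring. Without this change, step 3 cannot be carried out.
5. Add inverse-probability-of-censoring weights as a sensitivity analysis, because the decision to start treatment depends on risk.
6. Use the same definition in the Sample size calculation section, and say whether the 200 events refer to the training half or to both halves.

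The cost is revised wording, a different model and an additional censoring model. No new patients are needed. One condition is open: the article says that information on therapies is collected at follow-up, but not that start dates are. If starts are known only to the 6-month interval, some strokes and starts will fall in the same interval. The sponsor should confirm that the recorded data can order them, and state a rule for those that cannot be ordered.
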